### Study outcomes

#### Primary efficacy outcome

Change in mean 24-hour ambulatory SBP between baseline and 8 weeks of follow-up. Hypertension has been selected as the primary outcome measure because of its robust association with inadequate sleep and its well-documented association with CVD.

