### Sample-size calculation

The primary outcome is the mean difference in SBP reduction over the 8-week period between the two study groups. Our estimated minimum clinically meaningful effect size is 5 mm Hg, with an estimated standard deviation (SD) for SBP reduction of 8.3 mm Hg in the intervention group and 7.7 mm Hg in the control group, based on previous research
[31]. The minimum effect size is based on previous randomized controlled trials reporting a reduction in CVD with reductions in SBP of 5 mm Hg or greater, and the reduction in blood pressure with lifestyle interventions observed in previous trials
[31–33]. A 5.6-mm Hg reduction in blood pressure in the ADVANCE trial resulted in relative-risk reductions of 9% for major vascular events, and 18% for cardiovascular death
[34]. Based on a two-sample comparison of means at a significance level of α = 0.05 and power of 80% to detect a difference of 4 mm Hg (power of 90% to detect a difference of 5 mm Hg) between treatment arms, and an estimated 5% loss to follow-up, a per-group sample size of 67 participants will be required.

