### Statistical analysis plan

#### Descriptive statistics and baseline characteristics

Descriptive statistics will be used to describe the baseline characteristics of the study sample, the flow of trial participants, and the level of missing data for both predictor and outcome variables. All losses to follow-up and dropouts will be counted, and where possible, reasons documented. Categoric variables will be described by using frequencies and percentages. Histograms and boxplots will be used to evaluate the distribution of continuous variables and to identify any outliers or potential errors in the data, with follow-up verification if necessary from the case-report forms. For continuous variables, the mean and standard deviation will be used to describe the typical value and spread in the sample. For continuous variables that are not normally distributed, the median and interquartile range will be used to describe the typical value and spread in the sample. All tests of significance will be two-sided and conducted at an α = 0.05 for level of statistical significance.

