#### Statistical analysis

The primary analysis will use the on-treatment dataset for all outcomes. On-treatment is defined as those participants who completed at least one session of the online sleep intervention. A secondary analysis will use the intention-to-treat dataset, and a third, per-protocol analysis, will also be carried out for all outcomes, with postrandomization exclusions due to ineligibility, noncompliance, loss to follow–up, or missing data.

A linear mixed model will be used to compare changes in mean 24-hour ambulatory SBP (and other secondary outcomes) from baseline to 8 weeks after randomization. We will adjust for covariates associated with the intervention and the outcome as appropriate (for example, age, baseline SBP, baseline DBP, baseline SCI score). The selection of explanatory variables for inclusion in the final model will be based on clinical plausibility and variable selection routines, the LASSO, and regression trees. It will be assumed that missing data are missing at random and therefore accounted for in the mixed model. The validity of this assumption will be investigated by looking at the missing data patterns and by modeling the probability of missing data based on the explanatory variables available. The sensitivity of the missing value-generating mechanism to the choice of variables for inclusion and the final conclusions will be assessed by using multiple imputations via chained equations and predictive mean matching. Model checking will be performed by using suitable model diagnostics and residual plots. All statistical analyses will be performed by using the software packages SPSS version 21.0, R version 2.15.3 and Minitab version 16.2.

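### Covariates of the primary SBP model are to be chosen from trial data, partly by chance association with arm; the model should be fixed in advance with baseline 24-hour SBP always in it

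*Protocol article*

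**What the plan says.** The primary outcome (Primary efficacy outcome) is "Change in mean 24-hour ambulatory SBP between baseline and 8 weeks of follow-up". The Statistical analysis section gives the model: "A linear mixed model will be used to compare changes in mean 24-hour ambulatory SBP (and other secondary outcomes").

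Two sentences there govern its covariates:

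- The criterion for adjustment: "We will adjust for covariates associated with the intervention and the outcome as appropriate (for example, age, baseline SBP, baseline DBP, baseline SCI score"). The four variables are examples, not a list.
- The route to the final model: "The selection of explanatory variables for inclusion in the final model will be based on clinical plausibility and variable selection routines", with LASSO and regression trees named alongside.

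No unadjusted or fixed-covariate model is named as primary. Under Descriptive statistics and baseline characteristics, the test level is set: "All tests of significance will be two-sided and conducted at an α = 0.05 for level of statistical significance". The Randomization, Blinding, and Data collection and quality control sections keep the statistician blinded to assignment until the analyses are complete.

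**The concern.** Allocation is randomized 1:1, so no baseline covariate is truly associated with arm. A covariate that appears to be is showing chance imbalance. The phrase is the usual definition of a confounder in an observational study, and it does not carry over. What makes a covariate worth adjusting for here is that it predicts the change in SBP, whether or not the arms happen to differ on it. Read literally, the rule passes over a strong predictor whenever it is well balanced, and its variance then stays in the residual.

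The rest of the rule is open as well. Clinical plausibility, LASSO and regression trees can return different sets, and the Measurements section collects dozens of baseline variables for 134 participants. Baseline SBP, the natural covariate for a change in SBP, has no guaranteed place.

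At stake are the precision of the primary estimate and, to a lesser degree, how far its p value can be taken at face value. The Discussion makes a significant effect in this trial the condition for a larger Phase III trial, so the p value does feed a decision.

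**Working it through.** **1. The plan's own figure.** Inputs from Sample-size calculation: SDs 8.3 and 7.7 mm Hg, difference 4 mm Hg, two-sided α 0.05, power 80%, 5% loss.

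- SD = √((8.3² + 7.7²)/2) = √64.09 = 8.006.
- n = 2 × (1.960 + 0.842)² × 64.09 / 4² = 62.9, so 63 per group.
- 63 / 0.95 = 66.3, so 67 per group. This matches the plan.

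The plan states "power of 80% to detect a difference of 4 mm Hg (power of 90% to detect a difference of 5 mm Hg"). With 63 evaluable per group the normal formula gives 80.1% and 93.9%. This is an unadjusted two-sample comparison, so it neither supports nor contradicts any covariate rule.

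**2. What the arm criterion does to a strong predictor.** Under randomization the p value for a covariate's association with arm is close to uniform. If association means p < 0.2 (an assumption; the plan gives no threshold), any covariate, however prognostic, passes in only about 20% of trials.

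**3. What fixed adjustment is worth.** Assumptions, not document figures: 64 evaluable per arm, SD 8, and prognostic covariates correlated 0.4, 0.2, 0.1 and 0.1 with the change. SE = residual SD × √(2/64); power ≈ Φ(4/SE − 1.96).

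| Adjustment | Residual SD | SE | Power |
|---|---|---|---|
| None | 8.00 | 1.414 | 0.81 |
| Strongest covariate only | 8√(1 − 0.16) = 7.33 | 1.296 | 0.87 |
| All four | 8√(1 − 0.22) = 7.07 | 1.249 | 0.89 |

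Most of the gain comes from the one strong covariate.

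**4. Simulation of the selection rules.** Same assumptions, 12 independent candidates including those four, ordinary least squares on the change score in place of the mixed model; 8,000 null runs and 4,000 runs with a true 4 mm Hg difference.

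| Rule | Type I error | Power | Mean estimate (mm Hg) |
|---|---|---|---|
| No covariates | 0.049 | 0.80 | 4.00 |
| Four fixed covariates | 0.052 | 0.88 | 3.99 |
| One fixed LASSO rule, arm not used | 0.052 | 0.87 | 3.85 |
| Associated with arm and outcome (p < 0.2 each) | 0.040 | 0.81 | 3.90 |
| Smallest p of six covariate sets | 0.09 | 0.92 | 4.31 |

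The Monte Carlo standard error at 5% is √(0.05 × 0.95/8000) = 0.0024, so 0.040 is about four standard errors below nominal. The reason is visible in the null runs. Under the arm-and-outcome rule the estimates have SD 1.335, while the model SE is about 1.414 when nothing is selected. The rule removes the imbalances that move the estimate but leaves the prognostic variance of balanced covariates in the residual, so the SE is too large. Power falls by 0.88 − 0.81 = 0.07.

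**5. Second simulation.** With 128 subjects, 20 candidates (4 prognostic) and SD 8, the arm-and-outcome rule gave type I error 0.037, mean estimate about 3.84 and power 79%, against 86 to 87% with fixed baseline adjustment.

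**6. Upper bound under free choice.** With 20 to 35 candidates, single strategies (fixed, LASSO, a univariable screen on outcome, a screen on outcome or arm) gave 0.044 to 0.057. The smallest p of those four gave 0.078 to 0.083. With the six sets in step 4 it was about 0.09.

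**The case against.** **Selection does not by itself inflate type I error.** A reader might infer that LASSO or a tree makes the p value anti-conservative. The calculations do not show this: a single fixed LASSO rule gave 0.052, and the literal arm-and-outcome rule is conservative. This stands in full.

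**The 8 to 9% does not describe the plan.** It arises only if someone reports the smallest of several p values, and the protocol describes no such step. Most of the models in that comparison are not named in the protocol. A simulation of what is named (LASSO, a depth-2 tree, their union and their intersection; 128 subjects, 20 candidates, 800 runs) gave single-strategy error of 0.032 to 0.061. The smallest of the four gave 0.061, 0.048 and 0.075 at baseline-change correlations of 0.3, 0.4 and 0.5, with Monte Carlo error of about 0.008. The figure is therefore an upper bound only.

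**The statistician is blinded.** This does guard against choosing the favorable model, and LASSO or trees run on the outcome need no arm codes. It is incomplete: screening on association with the intervention needs at least coded groups, and an analysis set defined by at least one completed online sleep session tends to show which group is which.

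**Baseline SBP would rarely be lost.** In the same simulation LASSO kept it in 93 to 100% of runs and the tree in 80 to 99.9%, and clinical plausibility would also favor it. That is fair for those selectors. It does not answer the arm criterion in step 2 of the working, which ignores prognostic strength.

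**This is not a confirmatory trial, and the rule is not post hoc.** Correct. The Trial design section calls it Phase II and proof-of-principle, and the approach is announced in advance, though loosely.

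**The details belong in a fuller plan.** The candidate list, the penalty and the reconciliation of routines may well be there, and their absence is not the point. The arm criterion and the data-driven final model are stated in the article, so a fuller plan would have to replace them.

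**Conclusion.** The point holds in a limited form. The protocol states a covariate rule for the primary model that is unsound after randomization, and it leaves the final model to the data without guaranteeing baseline SBP. Followed literally, the rule loses efficiency and leans toward the null: type I error about 0.04, an estimate of about 3.8 to 3.9 for a true 4 mm Hg, and about 7 points of power lost against fixed baseline adjustment.

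These sizes rest on assumed correlations, independent candidates, a p < 0.2 screen in the 12-candidate run, and least squares in place of the mixed model. In that run the fixed set was also the truly prognostic one, which favors it; step 3 shows that one strong covariate alone gives most of the gain. The slight attenuation is not peculiar to the arm criterion, since the LASSO rule that ignored arm showed it too (3.85). The documents do not support a claim that the plan as written inflates the false-positive rate. It leaves room for that, to about 8 to 9% at most in these simulations, if a favorable model were picked.

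**What to change.** In the Statistical analysis section:

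1. State the primary model: 24-hour ambulatory SBP at 8 weeks (or its change) on arm, always adjusted for baseline 24-hour ambulatory SBP plus a short named list of baseline covariates already collected, for example age and the other variables the section now gives as examples. Say that baseline SBP means the ambulatory value, because office SBP is also recorded.
2. Delete the requirement that covariates be associated with the intervention. Choose them in advance on expected prognostic value.
3. Keep LASSO and regression trees for sensitivity or exploratory analysis, labeled as such.

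The cost is wording only: sample size, visits and data collection do not change. What is given up is any extra precision that a covariate chosen from the data might have added.

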#### Subgroup and sensitivity analyses

The primary outcome will be analyzed by subgroups based onAge (≥65 years versus <65 years)SexSeverity of hypertension at baseline (SBP 130 to 150 versus 151 to 160)Use of antihypertensive medication at time of entry into the trialIntroduction of antihypertensive medication during the trialSleep condition indicator score ≤5.9 versus >6.0Body mass index (BMI ≤25 versus >25)Employment statusConcomitant use of hypnoticsDepression, score ≥17 versus <17 on BDIAnxiety, score ≥22 versus <22 on BAIAdherence to the intervention

Statistical tests of interaction will be performed for all subgroup analyses. A sensitivity analysis will be performed to assess the influence of adherence to the intervention, on the estimated treatment effect. These analyses will use the on-treatment dataset.

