**Methods:**

*Trial design:* Randomized-controlled, two-group, parallel, blinded, single-center, Phase II trial of 134 participants. *Population and recruitment*: Primary prevention population of participants with hypertension (systolic blood pressure, 130 to 160 mm Hg; diastolic blood pressure, <110 mm Hg) and poor sleep quality in a community setting. *Intervention:* Multicomponent online sleep intervention consisting of sleep information, sleep hygiene education, and cognitive behavioral therapy. *Comparator:* Standardized cardiovascular risk factor and lifestyle-education session (usual care). *Primary outcome:* Change in mean 24-hour ambulatory systolic blood pressure between baseline and 8-week follow-up. Hypertension has been selected as the primary outcome measure because of its robust association with both poor sleep quality and cardiovascular disease. *Statistical analyses*: Intention-to-treat analysis by using a linear mixed model.

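### Interaction tests for six continuous baseline measures are tied to two-level cuts, which costs information on effect modification in a small trial; keeping the measures continuous is a cheap improvement to exploratory tests

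*Protocol article*

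**What the plan says.** The subgroup section analyses the primary outcome, change in mean 24-hour ambulatory SBP, by twelve factors. Six are continuous baseline measures cut in two: age at 65 years, baseline SBP at 150/151 mm Hg, SCI at 5.9/6.0, BMI at 25, BDI at 17 and BAI at 22. The last two appear in a run-together list as "score ≥17 versus <17 on BDIAnxiety, score ≥22 versus <22 on BAIAdherence to the intervention". The section then states that "Statistical tests of interaction will be performed for all subgroup analyses", and on the data to be used, "These analyses will use the on-treatment dataset".

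The measurements section lists all six among the baseline data at full scale. The statistical analysis section names some of them as continuous covariates ("for example, age, baseline SBP, baseline DBP, baseline SCI score"), but as examples for adjustment, not as interaction terms. The dose/response analysis under cointerventions concerns sessions completed, not these measures. No reason is given for any of the cuts.

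**The concern.** When a measure is on file at full scale, testing its interaction with treatment through a two-level version treats everyone on one side of the cut as alike. Unless the effect really jumps at the cut, this discards information, and more so when few participants fall on one side. Interaction tests are already weak in a trial sized for a main effect, so a null result from a cut version says even less about whether the measure modifies the effect.

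This is a method that the article states, not a detail left open: it fixes the cut points and attaches the interaction tests to the resulting subgroups. The point would hold even if every cut were exhaustive and well chosen.

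**Working it through.** **Inputs from the protocol article.** Total size: "Phase II trial of 134 participants". Attrition and group size: "an estimated 5% loss to follow-up, a per-group sample size of 67 participants will be required". SDs of SBP reduction: "8.3 mm Hg in the intervention group and 7.7 mm Hg in the control group". Two-sided α is 0.05 and allocation is 1:1.

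**The plan's own figure.** The article claims 80% power for 4 mm Hg and, in brackets, 90% for 5 mm Hg.
- Pooled SD = √((8.3² + 7.7²)/2) = 8.006 mm Hg.
- n per group for 4 mm Hg at 80% power = 2 × (1.960 + 0.842)² × 8.006² / 4² ≈ 62.9, so 63.
- 63 / 0.95 = 66.3, so 67. The stated 67 per group reproduces.
- With 63 per group, power for 5 mm Hg is about 94%, so the bracketed 90% is conservative.

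No figure is stated for the interaction tests.

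**Information kept after a cut.** For a linear interaction, the share kept is the squared correlation between the modifier and its two-level version. For a normal modifier with a fraction p beyond the cut, this is φ(z_p)² / [p(1 − p)].

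| Split | Kept | Lost |
|---|---|---|
| 50/50 | 64% | 36% |
| 70/30 | 58% | 42% |
| 80/20 | 49% | 51% |
| 90/10 | 34% | 66% |
| 95/5 | 22% | 78% |

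The shape of the distribution matters. A uniform modifier cut at its median keeps 75% and loses 25%. Skewed modifiers (exponential, or gamma with shape 2), plausible for BDI and BAI, lose about 35 to 60% over splits from 50/50 to 95/5.

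**Power.** Analysed N = 134 × 0.95 ≈ 127. The standard error of the interaction per SD of a continuous modifier is 2 × 8.0 / √127 = 1.42 mm Hg. The article gives no interaction size, so I assume that the treatment effect changes by 2 mm Hg per SD of the modifier. Noncentral t with 123 df gives:

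| Form of the modifier | Power |
|---|---|
| Continuous | 29% |
| Cut 50/50 | 20% |
| Cut 80/20 | 17% |
| Cut 90/10 | 13% |

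The gain from keeping the measure continuous is 9 to 16 percentage points.

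**Why 2 and not more.** If individual effects are independent of control response, the plan's SDs imply an SD of individual effects, from all sources together, of √(8.3² − 7.7²) = √9.6 = 3.1 mm Hg. A single linear modifier at 3 mm Hg per SD would take 9/9.6 = 94% of that variance, and at 4 it would exceed it (16 > 9.6). At 2 it takes 4/9.6 = 42%, which is already generous.

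**What the cut tests can detect.** The difference between subgroup effects detectable with 80% power is (1.960 + 0.842) × 1.42 / √(p(1 − p)). That is about 8 mm Hg at 50/50, 10 at 80/20 and 13 at 90/10, against the 4 mm Hg behind the main comparison.

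**The case against.** The strongest reply is that little hangs on this. Prespecified cut-point subgroups with interaction tests are common and contradict nothing else in the article. The secondary aims name only adherence and antihypertensive use as modifiers, and the primary comparison does not depend on these tests. The continuous version does not rescue them either: at 2 mm Hg per SD, 29% power still leaves a null result uninformative. If the effect truly changes at a threshold at the cut, the cut is the better form. All of this stands, and it limits the weight of the point.

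Several stronger readings are tempting but unsupported:
- **A fixed loss of a third to two thirds for every interaction.** That range needs a near-normal modifier, linear modification and splits from 50/50 to about 90/10. The article gives no distributions or splits.
- **Large power gains, up to about 43 points.** These need 4 mm Hg per SD (80% continuous against 37% at 90/10), which is hard to square with the plan's SDs. Dropping the independence assumption could allow a larger interaction, but nothing in the article supports one.
- **Phase III rests on these subgroups.** The discussion makes a later trial depend on a significant treatment effect and does not mention subgroups.
- **The upper BDI and BAI groups must be nearly empty.** The exclusions cover severe or recently changed illness. Participants on stable antidepressants remain eligible, and everyone is selected for poor sleep. Small cells are possible but not established.

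The reply that coding of the interaction term can be left to a fuller plan does not stand, because the article itself ties the tests to the cuts.

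**Conclusion.** The point holds as a modest one. Six continuous baseline measures are tested for effect modification through two-level cuts although the full-scale values are available. Under roughly linear modification and a near-normal modifier, this loses 36 to 66% of the information on the interaction for splits from 50/50 to 90/10, with less for a uniform modifier cut at its median and more for a more extreme split. At an assumed 2 mm Hg per SD, the cost is 9 to 16 points of power from a base of 29%. The 127 analysed is optimistic, because these analyses use the on-treatment dataset, and a smaller set lowers power for both forms. A reader should not infer that the change makes the tests conclusive or that the trial's main result is at risk. These are exploratory tests, and the change is a cheap improvement in their precision.

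**What to change.** In the subgroup section, state that the interaction tests for age, BMI, BDI, BAI, baseline SBP and SCI use a treatment-by-modifier term with the continuous baseline value in the 24-hour SBP model. Report the change in treatment effect per unit or per SD with its 95% CI, and keep the stated cuts only to display subgroup estimates. Factors that are categorical by nature, such as sex, employment status and use of antihypertensives or hypnotics, stay as they are.

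The cost is one sentence and no new data. The downside is an assumption of linear modification and possible leverage from a few high BDI or BAI scores. General residual plots are weak at detecting either in a sparse tail, so add a flexible term or an influence check. If there is a reason to expect a threshold at one of the cuts, state it and keep the cut for that measure.

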### Randomization

A randomization strategy using randomly permuted blocks of varying block size is being used, which allows the assignment schedule to be preplanned before participant recruitment. The randomization schedule is constructed by using a computer-generated list of pseudo-random numbers. A centrally administered, computer-generated randomization scheme is being used to assign individual participants randomly in a 1:1 ratio, to either the intervention or control groups. Once a participant is deemed eligible for trial entry and has provided written informed consent, a researcher assigns a unique study-identification number to the participant and contacts the online sleep intervention (Sleepio) team with the participant's name, their assigned participant number, and contact details (Email address and telephone number). The Sleepio team then assigns the participant to the next available randomization number on the list, corresponding to a particular treatment assignment (Sleepio intervention or control). Participants randomized to Sleepio receive a code via Email to access the online sleep intervention. The Sleepio team holds the central record of all participants who have been randomized, along with the corresponding randomization numbers and treatment-group assignments. All investigators at the HRB-CRFG, including the statistician, are blinded to participant treatment-group assignment. At the end of the trial, treatment assignments will be compared with the randomization list, to detect any incorrect assignments, and following completion of statistical analyses, all investigators and trial personnel will be unblinded.

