#### Cointerventions

Participants in this trial will ideally not receive any antihypertensive medications throughout the 8-week period. However, participants receiving up to two antihypertensive agents at the time of entry into the trial are eligible for inclusion, provided that no recent (within the previous 8 weeks) changes occurred in type or dose of antihypertensive medications and there are no planned change to antihypertensive medication over the next 8 weeks (during the trial). Note: in patients with mild hypertension and no history of CVD, current guidelines recommend an initial period of lifestyle intervention, consistent with our approach. Treating clinicians will be permitted to use clinical judgment in initiating and dose-adjusting antihypertensive therapies for both study groups during the 8-week trial, where appropriate. Participants who are stable on cardiovascular preventive therapies (no change in previous 3 months), such as lipid-lowering agents, antithrombotic therapies, oral hypoglycemic agents, and insulin will continue their usual treatment. Participants not taking these agents will be encouraged to avoid initiation of treatment with these agents, until the 8-week trial period has been completed. However, treating clinicians will be permitted to use usual clinical judgment in initiating and dose-adjusting such medications, where appropriate. Initiation and/or dose adjusting of cointerventions will be recorded and measured and accounted for using sensitivity analysis. Participant adherence to the intervention will also be measured, and adjusted for using sensitivity analysis. For example, we will analyze the data for evidence of a dose/response relation between degree of reduction in SBP and number of online sleep sessions completed.

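### Adherence and antihypertensive starts arise after randomization and do not belong among the interaction-tested subgroups; the adherence interaction cannot be estimated at all

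*Protocol article*

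**What the plan says.** The section on subgroup and sensitivity analyses lists twelve subgroup factors for the primary outcome. Most are baseline characteristics. Two are not: the introduction of antihypertensive medication during the trial, and adherence. The rule for the list has no exception: "Statistical tests of interaction will be performed for all subgroup analyses". The section adds a sensitivity analysis on how "adherence to the intervention" influences the treatment effect, and ends: "These analyses will use the on-treatment dataset".

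The Statistical analysis section defines that dataset: "On-treatment is defined as those participants who completed at least one session of the online sleep intervention". The Randomization section shows who can complete a session: "Participants randomized to Sleepio receive a code via Email to access the online sleep intervention".

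The Cointerventions section states: "Participant adherence to the intervention will also be measured, and adjusted for using sensitivity analysis". Its example is that "we will analyze the data for evidence of a dose/response relation between degree of reduction in SBP and number of online sleep sessions completed". The same section lets clinicians start or adjust antihypertensive drugs in either arm during the eight weeks, and says such changes will be recorded and handled by sensitivity analysis. Whether adherence influences the SBP change is also a secondary aim.

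**The concern.** A test of interaction asks whether a randomized contrast differs between groups that were fixed before treatment could act. Neither variable meets that condition.

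- **Adherence** has no counterpart in the control arm, so there is no control group within each adherence level.
- **Drug starts** may depend on on-trial SBP, which is what the intervention is meant to lower. Starters in the two arms are then selected differently.
- **Adjusting for adherence** conditions on something that exists only in one arm and may be tied to motivation and prognosis.
- **The dose-response** compares participants who chose to do more or fewer sessions.

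At stake is how a proof-of-principle trial is read when a phase III trial is decided. One planned test returns nothing, and the other analyses give numbers that look like treatment effects but are not randomized comparisons.

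**Working it through.** **The plan's own figure.** Sample-size section: SDs 8.3 and 7.7, two-sided alpha 0.05, 80% power for 4 mm Hg, 5% loss. The mean variance is (8.3² + 7.7²)/2 = 64.09. Then n = 2 × (1.960 + 0.842)² × 64.09/4² = 62.9, so 63, and 63/0.95 = 66.3, so 67 per group. This reproduces the plan. About 64 per arm remain evaluable (67 × 0.95 = 63.65). SD 8 is used below. Positive values are SBP reductions.

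**1. Treatment-by-adherence interaction.** Let T be arm and A adherence, with A = 0 in every control. Then T×A = A for everyone, and the columns [1, T, A, T×A] have rank 3 of 4. The same holds if A is a session count. In the on-treatment set as literally defined no control remains, the rank is 2 of 4, and even the treatment effect cannot be estimated.

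**2. Adjusting for adherence.** The plan hopes for adherence above 85%; take p = 0.85 as a proportion of adherent participants.
- Collinearity: corr(T, A) = √(p/(2−p)) = √(0.85/1.15) = 0.86. The variance inflation is 1/(1 − 0.739) = 3.8, so the standard error roughly doubles.
- Meaning: in the model 1, T, A the coefficient of T is the mean of intervention non-adherers minus the mean of all controls.
- Bias (assumed): with no treatment effect and correlation r between latent adherence and SBP reduction, the coefficient is −8r × 0.2332/0.15 = −12.4r. That is −2.5 mm Hg at r = 0.2, −3.7 at r = 0.3, and 0 at r = 0.
- If instead a 5 mm Hg effect acts only through adherence and adherence is unrelated to prognosis, the coefficient is about 0, while the intention-to-treat effect is 0.85 × 5 = 4.25.

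**3. Drug-start subgroup.** This model has rank 4 of 4, so it can be estimated. The start rates, triggers and drug effects below are assumptions; the documents give none.

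*Sharp trigger:* uniform effect 4, with the 15% of controls whose SBP change is worst starting, and the same trigger in both arms. The cut is 1.036 SD in controls and 1.036 + 4/8 = 1.536 SD in the intervention arm, so 6.2% start there. The mean reductions before any drug effect are:
- Non-starters: 4 + 8 × 0.1225/0.9378 = 5.05 against 8 × 0.2332/0.85 = 2.19, an effect of 2.85.
- Starters: 4 − 8 × 0.1225/0.0622 = −11.76 against −8 × 0.2332/0.15 = −12.44, an effect of 0.68.
- Gap: 2.2. A constant drug effect cancels within starters.

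*Noisier trigger:* simulation of 1,000,000 with baseline SBP mean 145 and SD 8, trigger noise SD 5, drug effect 8, and three assumed trigger levels.

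| True effect | Start %, control / intervention | Non-starters | Starters | Gap |
|---|---|---|---|---|
| 4 | 34.4 / 23.4 | 3.19 | 2.77 | 0.4 |
| 4 | 20.9 / 12.9 | 3.40 | 2.64 | 0.8 |
| 4 | 11.2 / 6.2 | 3.59 | 2.53 | 1.1 |
| 5 | 34.3 / 20.9 | 4.00 | 3.41 | 0.6 |
| 5 | 21.0 / 11.3 | 4.23 | 3.30 | 0.9 |
| 5 | 11.2 / 5.3 | 4.48 | 3.27 | 1.2 |

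*At trial size:* with 64 per arm, effect 4, 15% of controls starting and drug effect 6, the interaction reached p < 0.05 in about 1% of simulated trials with the sharp trigger, 2% with trigger noise SD 4 and 3% with noise SD 8. About 64 × 0.15 = 10 controls and 64 × 0.062 = 4 intervention participants would be starters.

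**4. Dose-response.** By Fisher z with n = 64 and an inert course, an assumed confounding correlation of 0.2 gives 0.203 × √61 = 1.58 and a significant result with probability 0.35. For 0.3 the figures are 2.42 and 0.68. With no confounding it is 0.05.

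**The case against.** These are secondary, exploratory analyses in a phase II trial. The exclusion of planned drug changes, and of diabetes and renal impairment, should keep drug starts few. Cointerventions already have a planned sensitivity analysis. The dose-response is given only as an example of a sensitivity analysis. All of this stands and limits the weight of the point, but it does not make the adherence interaction estimable or turn drug starters into a valid subgroup.

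Four stronger readings are tempting and not supported:

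- *The trial would probably declare false effect modification by drug start.* At 64 per arm the simulated rate is below the nominal 5%. The distortion lies in the estimates.
- *A spurious dose-response is likely.* The 0.35 and 0.68 follow from correlations that the documents do not supply.
- *The dose-response is presented as causal, or as the answer to the secondary aim on adherence.* The article makes neither statement.
- *All the listed subgroup factors are unsound.* Interaction tests on baseline factors such as age and sex are legitimate. Their difficulty is the assigned dataset, which by its definition holds no controls. If the intention was to keep all controls and drop only non-starters of the course, the adherence interaction still has rank 3 of 4, and one arm has been selected after randomization.

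**Conclusion.** The point holds for two listed subgroup factors and for the adherence adjustment. That the adherence interaction cannot be estimated is a matter of algebra and needs no assumption. The bias from adjusting for adherence arises when adherence is related to prognosis; without that relation, adjustment can still remove a real effect that works through adherence. For drug starts, both subgroup estimates fell below the true effect in every scenario, with a gap of 0.4 to 2.2 mm Hg; this rests on starts following on-trial SBP and on the assumed start rates. The dose-response can be reported, but only as an association within the intervention arm. The sample size is unaffected, and these analyses do not enter the primary test. The matter should be corrected but does not threaten the trial.

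**What to change.** 1. Remove adherence and drug introduction from the interaction-tested list. Keep only factors measured before randomization, and specify that hypnotic use is taken at baseline.
2. Run the subgroup tests on all randomized participants as allocated, not on the on-treatment dataset.
3. Replace adjustment for adherence with a complier-average causal effect, using randomization as the instrument (two-stage least squares). State the exclusion restriction: allocation affects SBP only through taking up the course. At 85% adherence the estimate is about the intention-to-treat effect divided by 0.85, so 4 mm Hg becomes 4/0.85 = 4.7, with an interval wider by about 1/0.85 = 1.18.
4. Label the sessions-SBP relation as descriptive within the intervention arm.
5. Handle drug starts only in the cointervention sensitivity analysis already planned, set around the intention-to-treat estimate, for example by adding back a stated range of drug effects. The abstract names intention-to-treat as the analysis, whereas the Statistical analysis section makes on-treatment primary and intention-to-treat secondary; that needs reconciling so that this anchor is clear.

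The cost is revised wording and a few lines of code, with a wider interval for the complier-average estimate. No new data and no change in patient management are needed.
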